### Study Setting

This study will use a two-armed randomized-controlled trial design to compare the intervention group (BMS group) and control group (Tea break group). Researchers will promote the program in all 24 ICCMWs in Hong Kong and eligible participants will be recruited from the ICCMWs.

### Eligibility Criteria

This study welcomes both professionals (such as social worker, occupational therapist, and nurse) and supporting staff (such as peer support worker and administration). However, to ensure the attendance rate, only full-time staff are included while freelance or part-time workers will not be recruited in this study.

#### Intervention

Based on the successful experience of the pilot study, each session of the brief daily BMS intervention will run about 15 min on each working day and contain three standardized sections:

(1)Cooling down (about 4 min): It usually functions as the first step in spiritual or religious practices. The main purpose is to remind practitioners to bring their awareness to the present moment. In this way, they may build a connection with their body, mind and the environment they present at the moment (Ng et al., 2017). Examples to serve this objective include sitting on the floor or chair silently, counting the breath in and out. It is also helpful to play soft music or natural sounds, like birds sing or sounds of waves. The facilitator may spontaneously pick one of these practices in each group session.(2)Proverb sharing (about 8 min): Almost every culture has many proverbs, also known as mantras or sayings, using a simple sentence to provide life advice and philosophy. The group leader will prepare one positive sentence related to meanings of life, in order to provoke reflection and discussion within the group. Some examples are “*When slowing down, we can see the direction of cloud*,” and “*Compared with advance, compromise usually needs more courage and wise.*”The facilitator will deliver the sentence to each member in paper or through a cell phone. In the beginning, all participants, including the facilitator read this sentence out together. And then all members reflect it in silence for about 1 min. Thereafter, they will share their view about the sentence freely in the group. The aim of this activity is to stimulate thinking about purpose and meaning of life.(3)Energy activity (about 3 min): This activity serves as an ending ritual for the group with the purpose of provoking positive energy, enabling members to revitalize after the group, and fostering a mutual care atmosphere among the members. Some samples can be physical exercise, stretching, singing an inspirational song or interaction movement, such like mutual massage or hugging game. Regarding the physical contact, cultural sensitiveness should be borne in mind. The group leader may choose one of these exercises freely to end up a group session.

Because the activities in the three sections are standardized and fairly straightforward, the facilitators will be chosen from group members and given some prior training. Specially developed group activities toolkits will be provided to the facilitators.

### Participants and Sample Size Calculation

In light of the findings of the pilot trials, an effect size is assumed at a moderate level of 0.4. For a 2-arm RCT with power at 90%, significance level at 0.05, and allowing for a 10% attrition rate (dropout rate in pilot studies was zero), a sample size of 75 per arm is needed (G^∗^Power software version 3.1, Franz Faul, University of Kiel, Germany). Totally 150 participants will be required. Assuming an average of around 8 participants per group, a total of 9 pairs of intervention and control groups will be needed. Each study site, an ICCMW, will host a pair of intervention and control groups. Thus, a totally 9 study sites are needed.

The other consideration is the variability among the 24 ICCMWs in Hong Kong. They are run by 11 NGOs with a rather diversified background. For example, some of these NGOs are more experienced in mental health services, and some are bigger and more well-established. To reduce the bias at the study-site level, instead of only randomly selecting 9 of them, we aim to invite all the 24 ICCMWs to participate in the study. Assuming a conservative response rate of 60%, about 14 ICCMWs will join. At each site, a pair of intervention and control groups will be run. Each group will have about 8 participants. Thus, there will be a totally about 224 participants randomly assigned to either an intervention or a control group.

### Recruitment Strategy

There are a totally 24 ICCMWs in Hong Kong. Each ICCMW has around 30 mental health workers. Both PI and co-I’s are experienced mental health social work researcher/practitioners and have a long-term collaborative relationship with the NGOs providing mental health services in Hong Kong. The PI is also the Consultant of the Mental Health Social Work Chapter of the Hong Kong Social Workers Association. The Chapter, with most members from ICCMWs, is concerned about the chronic stress and lack of emotional support experienced by community mental health workers. With a neutral, academic affiliation, the PI and co-I’s are in a good position to invite ICCMWs to participate in the study.

By means of computer-generated random numbers, ICCMWs will be invited to participate in the study one by one. The PI and co-I’s will initiate meeting and site visit with each ICCMW according to the sequence generated by computer. If an ICCMW agrees to join the study, the PI and co-I’s will hold a briefing session for all the mental health workers of the Center and invite them to participate in the study. Those showing interest and providing informed written consent will be randomly assigned to either an intervention or control group at a 1:1 ratio with the aid of computer-generated random numbers. The recruitment process will continue with all the 24 ICCMWs.

### Procedures

In order to examine the course of changes in burnout and engagement, the intervention period is extended from 1 month in pilot trials to 3 months in the proposed study. The post-intervention follow-up period is also extended to 3 months. Measures will be taken at baseline (T0), and then at monthly intervals (T1–T6). All questionnaire surveys will be administered by the research assistant of the study.

According to the experience of pilot trials, frontline professionals such as social workers, occupational therapists and nurses are good facilitators for the intervention groups. A 1-h training session suffices in introducing new facilitators to the intervention. A member of the research team will sit-in the meetings of each new group in the first week, and provide feedback to the facilitator. Afterward, to ensure treatment fidelity, a member of the research team will visit the group biweekly, until the end of intervention.

During the 3-month intervention period, the trained facilitator will run the brief daily BMS group in a quiet room at the site every workday, normally 5 times a week except when there are public holidays. At each site, the facilitator and participants may decide on their preferred time slot on a day for the BMS group that fits their work schedule. It can be in the morning, at noon or in the afternoon, and the exact meeting time can be changed during the 3-month intervention period if the group prefers. The facilitator will keep an attendance record of participants for statistical purpose.

To control for the social gathering effects of the experimental group, a control group in the format of daily 15-min tea break will be organized in parallel at the same site on every workday during the 3-month intervention period. A participant of the control group will be assigned as the coordinator who will take care of the basic logistics, such as room and materials booking, time keeping, and keeping an attendance record of participants. The tea-break is to be conducted in a quiet room provided with the usual drinks and snacks available for staff at the site. The tea-break is unstructured. During the 15 min, participants are free to enjoy the drinks and snacks, and interact with other group members. Similar to the intervention groups, each control group may decide on their preferred time slot on a day for the tea-break that fits their work schedule. The same set of questionnaires will be administered on participants of each control group by the research assistant of the project at baseline (T0), then at monthly intervals (T1–T6). Figure 1 CONSORT diagram depicts the flow of the trial.

**FIGURE 1 F1:**
[figure not shown]
CONSORT diagram of intervention and active control groups and data collection points.

### Outcomes Measures

Measures of the related variables are summarized in Table 1 below. In line with the study’s objectives, primary outcome variables are work burnout and engagement. Since the intervention adopts a multidimensional BMS orientation, multiple somatic complaints, positive and negative affect, and daily spiritual experience are included as secondary outcome variables. Also included as secondary outcome variables are worker behavior, including overtime hours, sick leave, and injuries at work.

**TABLE 1 T1:** Variable table.

**Variable/instrument**	**Content of the instrument**	**Data type**
**Primary outcome variables**		
**(1) Demographics** ◆ Self-report items	Age, gender, marital status, family composition, education and professional qualification, religious belief	Ordinal and Nominal
**(2) Work burnout** ◆ Copenhagen Burnout Inventory-Chinese Version (Fong et al., 2014)	19-item self-report scale with 3 sub-scales: personal burnout, work-related burnout, and client-related burnout	Interval
**(3) Work engagement** ◆ C-UWES (Fong and Ng, 2012)	9-item self-report scale with 3 factors: Vigor, Dedication, and Absorption	Interval
**Secondary outcome variables**		
**(1) Multiple somatic symptoms** ◆ Physical Distress subscale of the Body-Mind-Spirit Well-Being Inventory (Ng et al., 2005)	14-item self-report scale	Interval
**(2) Positive affect** ◆ Positive Affect subscale of the Body-Mind-Spirit Well-Being Inventory (Ng et al., 2005)	8-item self-report scale	Interval
**(3) Negative affect** ◆ Negative Affect subscale of the Body-Mind-Spirit Well-Being Inventory (Ng et al., 2005)	11-item self-report scale	Interval
**(4) Daily spiritual experience** ◆ Chinese Daily Spiritual Experience Scale (Ng et al., 2009a)	16-item self-report scale	Interval
**(5) Collective psychological ownership** ◆ Chinese Collective psychological ownership Scale (Ng and Su, 2018)	7-item self-report scale	Interval
**(6) Worker behavior** ◆ Self-report items	Overtime hours, sick days taken off from work and injuries at work in the past month	Interval and ordinal

### Data Analysis

Both completers and intention-to-treat analysis will be performed. In the intention-to-treat analysis, missing data will be handled by ‘last observation carried forward.’ With a 2-arm RCT design, the efficacy of the intervention will be examined by repeated measures MANOVA on both primary and secondary outcome variables. Partial eta-squared (η^2^) values are computed to assess the effect sizes; values of 0.02, 0.13, and 0.26 suggest small, medium, and large effect sizes, respectively (Pierce et al., 2004). To investigate within group effects, serial trend analysis from T0 to T6 will be conducted on the outcome variables. In the case of work engagement, changes in a range of scores from T0 to T6 will also be examined. The associations between primary and secondary outcome variables will be explored by correlational and multiple regression analyses.

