In the context of Hong Kong, the extreme work-life imbalance is common and adds to the stress of workers (Ng et al., 2009b, p. 179). In many work teams, overtime work is a norm rather than the exception, and members are under pressure to conform at the cost of sacrificing some personal and family time. In the welfare sector, additional stresses include relentless pressure on securing funding, fulfilling elaborative documentation procedures, meeting the increasing expectations of service users, and in some cases, dealing with unfriendly resistance from local residents. There is a widespread feeling among social service workers in Hong Kong that job burnout has become an epidemic (Ng, 2008). A worrying indicator is persistently high staff turnover, with double-digit annual staff turnover rate being a norm.

The proposed study focuses on the well-being of community mental health workers. In 2010 the Social Welfare Department, Hong Kong SAR government restructured the fragmentized community mental health services around a new mega, one-stop service named ICCMW (Ng, 2015, p. 8). The scope of service of ICCMW is extremely wide, ranging from education and prevention to treatment and rehabilitation. Targeted service users include people suffering from SMI and common mental disorders, as well as healthy people in the community. Operational modes include rapid response to psychiatric emergency, time-limited casework, long-term support for people with chronic SMI, day center and community development. As a result of the service restructure, a total of 24 ICCMWs were established covering the whole territory of Hong Kong, which has a population of over 7 million. The 24 ICCMWs are manned by a totally of about 700 mental health workers. Most of them have a background in social work, nursing and occupational therapy. Charged with such a wide scope of responsibility, ICCMWs are overstretched to achieve all the goals and pledged service outputs (Ng, 2015, p. 36). Moreover, due to the nature of work, community mental health workers often spend much time in performing home visit on their own. This makes it difficult to create a supportive teamwork environment. As a result of all these factors, community mental health workers are under chronic stress and are vulnerable to burnout. They need continued support for sustainable emotional capacity and work engagement.

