## Research Methods and Design

### Research Aim and Objectives

The overall aim of the proposed research is to pursue the further rigorous trial of the brief daily BMS program, which demonstrated good potentials in the pilot studies. The specific objectives are:

(1)To evaluate the efficacy of the brief daily BMS program in reducing burnout and enhancing engagement for community mental health workers;(2)To examine the trajectory of burnout, especially exhaustion, during a 3-month intervention and 3-month post-intervention periods; and(3)To examine the trajectory of engagement during a 3-month intervention and 3-month post-intervention periods.

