### Hypotheses

In light of the literature and findings of the pilot trials, we have the following hypotheses:

H1: Reduction of burnout will be observed within the 3-month intervention period;H2: Rebound of burnout will be observed within the 3-month post-intervention period;H3: A narrowing of range in work engagement will be observed within the 3-month intervention period; andH4: A widening of range in work engagement will be observed within the 3-month post-intervention period.

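### Last observation carried forward assumes burnout stops changing once a worker is lost, while the trial sets out to measure a fall to T3 and a rebound by T6

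*Protocol article*

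**What the plan says.** The protocol article fixes the rule for missing data under Data Analysis: "In the intention-to-treat analysis, missing data will be handled by" last observation carried forward. The same section opens with "Both completers and intention-to-treat analysis will be performed", and names no other way of treating missing scores. It tests efficacy by repeated-measures MANOVA and plans a within-group trend analysis over T0 to T6.

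The course over time is itself the research question. Under Research Aim and Objectives, objective 2 is "To examine the trajectory of burnout, especially exhaustion, during a 3-month intervention and 3-month post-intervention periods" and objective 3 is "To examine the trajectory of engagement during a 3-month intervention and 3-month post-intervention periods". Under Hypotheses, H1 expects burnout to fall during the intervention, H2 reads "Rebound of burnout will be observed within the 3-month post-intervention period", and H4 reads "A widening of range in work engagement will be observed within the 3-month post-intervention period".

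Three further statements bear on the point. The account of the pilot in the Background reports that the gains seemed to fade one month after the program ended. The sample size section allows for 10% attrition and notes that the pilots, which lasted one month, had none. The Background describes "double-digit annual staff turnover rate being a norm" in the Hong Kong welfare sector.

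**The concern.** LOCF is a model for the missing scores, and the model says that nothing changes after the last visit. The protocol predicts change in both halves of the study, and its own pilot supports the second half of that prediction.

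What happens to a lost worker's score depends on the last visit attended:

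- Last seen at T0, T1 or T2: the full T3 reduction is never recorded, and no rebound is recorded.
- Last seen at T3: the whole T3 benefit is carried to T6, and no rebound is recorded.
- Last seen at T4 or T5: the score stops part-way through the rebound.

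If the mean course is as hypothesised, each case flattens T3 to T6. Early loss also reduces the T3 effect. At T6 the carried scores leave some benefit that is no longer there. If the control arm is flat, LOCF does not move its mean, so this residue appears as a difference between arms even with equal dropout. In addition, the filled-in scores enter the analysis as if they had been measured, so the stated precision is too good.

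**Working it through.** The plan gives no figure for the effect of LOCF, so there is nothing of its own to reproduce. The check is an expected-value calculation.

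**Inputs from the protocol article**
- Effect size 0.4 and attrition d = 10% (sample size section).
- Visits T0 to T6, monthly, with the intervention ending at T3 (Procedures).

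**Assumptions, not in the documents**
- The 0.4 is a standardised mean change reached at T3.
- The path is linear: 0, -0.133, -0.267, -0.400, -0.267, -0.133, 0 at T0 to T6.
- Leaving is unrelated to outcome. Four timings of the last visit are tried.
- Attrition of 20% and 30% is tried to show how the bias grows.

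**Formula.** At each visit, LOCF mean = (1 - d) × true mean + d × mean carried score of leavers. Rebound = T6 mean - T3 mean; the true value is 0.40.

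**Worked case: d = 10%, last visit spread evenly over T0 to T5**
- Leavers' mean at T3: (0 - 0.133 - 0.267 - 0.400 - 0.400 - 0.400)/6 = -0.267.
- LOCF mean at T3: 0.9 × (-0.400) + 0.1 × (-0.267) = -0.387.
- Leavers' mean at T6: (0 - 0.133 - 0.267 - 0.400 - 0.267 - 0.133)/6 = -0.200.
- LOCF mean at T6: 0.9 × 0 + 0.1 × (-0.200) = -0.020.
- Rebound: -0.020 + 0.387 = 0.367.

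**All timings at d = 10%**

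| Last visit of leavers | T3 mean (true -0.400) | T6 mean (true 0) | Rebound (true 0.400) | Shortfall |
|---|---|---|---|---|
| T0 to T5, evenly | -0.387 | -0.020 | 0.367 | 8.3% |
| T3 | -0.400 | -0.040 | 0.360 | 10% |
| T0 to T2, evenly | -0.373 | -0.013 | 0.360 | 10% |
| T3 to T5, evenly | -0.400 | -0.027 | 0.373 | 6.7% |

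Across the same four timings the rebound is 0.320 to 0.347 at 20% and 0.280 to 0.320 at 30%.

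**Dependence on a full rebound.** A leaver last seen at or before T3 misses the whole rebound, whatever its size. With a linear rise, one last seen at T4 misses two thirds and one last seen at T5 misses one third. For T3 to T5, evenly, the average share missed is (1 + 2/3 + 1/3)/3 = 2/3, and 10% × 2/3 = 6.7%. The percentage shortfall therefore stays the same if the rebound is only partial; the absolute shortfall gets smaller.

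**Spread of engagement (H4).** Assume an SD of 0.8 at T3 and 1.0 at T6, equal means, and leavers held at their T3 scores. The T6 SD under LOCF is √(0.9 × 1.00 + 0.1 × 0.64) = √0.964 = 0.98 instead of 1.00. A maximum-minus-minimum range moves only if leavers are among the extreme scorers.

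**The case against.** The strongest reply is that the damage is small and partly covered. At the attrition the protocol plans for, the rebound is short by 0.03 to 0.04 SD. The completers analysis is planned alongside, and where leaving is unrelated to outcome, which is the case computed above, it recovers the true 0.40. The error also works against H1 and H2, so it does not flatter the trial's own predictions. All of this stands and limits the weight of the point. It does not rescue LOCF: completers are unbiased only if leaving is unrelated to outcome, and in a burnout trial that is the doubtful assumption.

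Some stronger readings are tempting, and the document does not support them:

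- **All leavers are frozen at an intervention-period level.** This holds only for those last seen at T1 to T3.
- **The timing of loss sets the direction of the bias.** In every timing computed the rebound shrinks, and the T3 effect shrinks or is unchanged. Timing sets the size. A change of direction would need leaving to be related to burnout, which is not quantified here.
- **H4 is seriously biased.** The effect on the SD is small, and the effect on a range may be nil.
- **Turnover will push attrition well above 10%.** The turnover figure is annual and sector-wide. An assumed 10 to 20% a year is roughly 5 to 10% over six months, in line with the allowance.
- **Workers who stop attending will no longer be surveyed.** The Procedures section has the research assistant administer the questionnaires monthly through T6 and does not tie them to attendance.
- **Scores are expected to change every month along a set path.** H1 and H2 speak of change within each three-month period. The linear path and the full return to baseline are assumptions of this check.

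**Conclusion.** The point holds, as a modest bias from a rule that the protocol states outright. It is not a gap that an analysis plan would be expected to fill. LOCF contradicts H1, H2 and objective 2. The same logic reaches the engagement trajectory in objective 3, with a small and uncertain effect on H4.

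At 10% attrition, and under the assumed linear path with uninformative leaving, the rebound is understated by 7 to 10%. The T3 effect falls from 0.400 to 0.387 with even dropout, or to 0.373 if all loss occurs during the intervention. The false benefit at T6 is 0.02 SD with even dropout, and ranges from 0.01 to 0.04 SD by timing. These figures rest on the assumed path and dropout timing; the document supplies only the 0.4 and the 10%. The overstated precision is certain in direction, but its size is not computed.

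**What to change.** In the Data Analysis section, delete LOCF. Make the primary intention-to-treat analysis a likelihood-based repeated-measures mixed model that uses every observed T0 to T6 score of all randomised workers. It is valid if scores are missing at random and needs no filled-in values. For this analysis it takes the place of the repeated-measures MANOVA, which needs a complete set of visits per worker. State that the completers analysis is a sensitivity analysis only.

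Optionally, add one delta-adjusted sensitivity analysis, in which leavers' unobserved scores are shifted by a stated amount, to cover leaving that is related to burnout.

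The cost is a change of wording and slightly more analysis work. Design, sample size and data collection are unaffected.

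### The only between-arm efficacy test is an omnibus repeated measures MANOVA, with no deciding contrast and no T0 adjustment; it does not directly answer H1 and is usually weaker than a T0-adjusted T3 comparison

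*Protocol article*

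**What the plan says.** - **Test (Data Analysis).** "With a 2-arm RCT design, the efficacy of the intervention will be examined by repeated measures MANOVA", applied to the primary and the secondary outcomes alike. This is the only between-arm analysis in the section. The trend analysis over T0 to T6 that follows is described as a within-group analysis.
- **Waves (Procedures).** "Measures will be taken at baseline (T0), and then at monthly intervals", up to T6. That gives one baseline, three intervention waves (T1 to T3) and three follow-up waves (T4 to T6).
- **Outcomes (Outcomes Measures).** "primary outcome variables are work burnout and engagement".
- **Expected course (Hypotheses).** H1 has burnout falling during the 3-month intervention. H2 has it rebounding over the next three months. H3 and H4 concern the range of engagement scores.
- **Size (Participants and Sample Size Calculation).** "an effect size is assumed at a moderate level of 0.4", and "For a 2-arm RCT with power at 90%, significance level at 0.05, and allowing for a 10% attrition rate", from which "a sample size of 75 per arm is needed". The planned total is 224. The effect of 0.4 is tied to no outcome, wave or contrast.

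**The concern.** Objective 1 is to show that the programme reduces burnout, and H1 places that reduction in the intervention period. Together they call for a directed comparison of the arms at or near T3. An arm-by-time MANOVA asks whether the two mean profiles differ in shape anywhere across seven waves. A significant result does not say in which direction or at which wave, and the partial eta-squared planned as its effect size is unsigned. Further contrasts would be needed to answer the trial's question, and the protocol names none between arms.

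The test also spreads its sensitivity over waves where the protocol itself expects the benefit to fade. Comparing each later wave with T0 is less efficient than using T0 as a covariate. At stake are power for the hypothesised effect and a clear statement of what a positive result would mean.

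**Working it through.** **1. The plan's own figure.** A two-sided comparison of two means at 0.4 SD, alpha 0.05 and 90% power needs n = 2(1.960 + 1.282)² / 0.4² ≈ 132 per arm, or 147 after allowing for 10% attrition. The stated 75 is not reproduced this way. That is a separate matter, but it means no test in Data Analysis can be recognised behind the sample size. The main comparison therefore uses the planned recruitment: 224/2 = 112, and 112 × 0.9 ≈ 101 completers per arm. The 75 case is shown as well (75 × 0.9 ≈ 68).

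**2. Assumptions not in the protocol.** SD 1. The control arm is flat. The burnout effect rises linearly to 0.4 at T3, then returns linearly to 0 at T6 (full rebound) or to 0.2 (half rebound). Correlation ρ between any two waves is equal: 0.5, 0.6 or 0.7. There is no clustering by group or site. One outcome is modelled.

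**3. Omnibus arm-by-time test (6 df).** Let δ be the six effects measured as changes from T0. With equal correlation the noncentrality is

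λ = (n/2) × [Σδ² − (Σδ)²/7] / (1 − ρ), referred to F(6, 2n − 7).

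- Full rebound: Σδ² = 0.338 and Σδ = 1.2, so the bracket is 0.338 − 0.206 = 0.132. At ρ = 0.5, λ = 50.5 × 0.132 / 0.5 ≈ 13.3.
- Half rebound: Σδ² = 0.471 and Σδ = 1.6, so the bracket is 0.471 − 0.366 = 0.105. At ρ = 0.5, λ ≈ 10.6.

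**4. Single contrasts at T3.** The noncentrality is 0.4 / √(2v/n), with v = 2(1 − ρ) for the change score and v = 1 − ρ² when T0 is a covariate. At ρ = 0.5 and n = 101 these are 0.4/√(2/101) = 2.84 and 0.4/√(1.5/101) = 3.28.

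**5. Power, 101 per arm.**

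| Test | ρ = 0.5 | 0.6 | 0.7 |
|---|---|---|---|
| Omnibus, full rebound | 78% | 87% | 96% |
| Omnibus, half rebound | 66% | 77% | 90% |
| T3 change score | 81% | 89% | 96% |
| T3 adjusted for T0 | 90% | 94% | 98% |

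The two T3 rows do not depend on the rebound. With 68 per arm and full rebound, the omnibus has 56 / 68 / 82% and the adjusted T3 contrast 76 / 83 / 90%.

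**6. Where the gap comes from.** With full rebound and ρ = 0.5, moving from the omnibus to a T3 change score gains about 3 points, and adjusting for T0 gains about 9 or 10 more. At ρ = 0.7 the first step gains nothing. Most of the full-rebound gap is therefore baseline adjustment. With half rebound and ρ = 0.5, the first step is worth about 15 points (66 to 81%).

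**7. Sensitivity.**
- *Both primary outcomes in one MANOVA* (12 df; no mean shift in engagement; correlation −0.3 between outcomes; full rebound; 101 per arm): 68% at ρ = 0.5 and 92% at ρ = 0.7. If engagement shifts equally in the opposite direction: 85% and 99%.
- *Equal correlation 0.8, full rebound:* the omnibus and the adjusted T3 contrast tie (99.6 v 99.7%).
- *Immediate, sustained effect, first-order autoregressive correlation 0.8:* the omnibus is stronger (94 v 91%). With 68 per arm, autoregressive correlation 0.9 and the two-outcome test, it is again stronger (96 v 92%).

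**The case against.** The strongest reply is that an article may leave the primary time point, covariates and follow-up contrasts to an analysis plan that is not shown, and that Objectives 2 and 3 concern trajectories, for which a profile test is natural. The first part carries weight: silence on detail is not itself a fault. But the choice of MANOVA as the efficacy test is fixed in the protocol, and the point is about that choice. The second part supports keeping the trajectory analyses. It does not make an undirected test the answer to Objective 1 and H1.

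The power argument is also open to challenge. The direction of the difference can reverse (step 7), and with full rebound little of the loss comes from the omnibus form itself (step 6). Both stand, and they limit the claim to usually less powerful under the protocol's expected course.

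A reader might infer more than the text supports:

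- *That the trial was sized for the T3 effect.* The sample-size section names no wave or outcome for 0.4.
- *That T0 is declared a MANOVA outcome, or that the baseline is wasted.* T0 is named only for the within-group trend and the engagement range. An arm-by-time test uses T0 as its reference, so the loss is one of efficiency.
- *That the efficacy test is the arm effect averaged over all waves*, which would have only 29 to 36% power under full rebound at 101 per arm. Nothing makes that term the deciding one.
- *That the false-positive rate is 9 to 10%, or that subscales share alpha.* The rate would apply only if burnout and engagement were tested separately at 5% each, which the protocol does not say. A single joint test holds its own 5%. Subscales are listed as instrument content, and no subscale tests are stated.

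**Conclusion.** The point holds in limited form. The protocol fixes an omnibus repeated measures MANOVA as its only between-arm efficacy test, without a deciding contrast or adjustment for T0. On the natural arm-by-time reading, that test does not directly answer whether burnout was lower during the intervention.

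If burnout falls by T3 and then rebounds, the test gives up roughly 2 to 13 percentage points of power against a T0-adjusted T3 contrast with full rebound, and roughly 8 to 24 points with half rebound (101 per arm, equal correlation 0.5 to 0.7). These sizes rest on correlations and an effect course that the protocol does not give, on a flat control arm and on ignoring clustering. They illustrate the loss and do not estimate it for this trial. The lack of a directed answer to H1 does not depend on those assumptions. This is an inexpensive improvement that should be made; it does not invalidate the trial.

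**What to change.** In Data Analysis, name the primary efficacy analysis as the between-arm difference in the CBI burnout score at T3, adjusted for the T0 score and site, from a longitudinal mixed model (or ANCOVA) in all randomised participants. Report it as a signed difference with a confidence interval.

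Analyse engagement with the same baseline-adjusted model. Because the protocol lists burnout and engagement together as primary, any testing order between them is the investigators' decision and should be stated. A model of means does not test the change in range in H3 and H4, so the range analysis should stay. Keep the T0 to T6 trajectory analyses and the MANOVA as supportive.

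The cost is a change of wording, since all the data are already collected under the schedule. The downside is that effects at waves other than T3 become secondary, and if the true effect were immediate and sustained with high serial correlation, the T3 contrast could be slightly less powerful than the omnibus.
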